**Methods:**

This is a pilot quasi-experimental study assessing feasibility and viability, with a nonrandomized control group, to be conducted in the Emergency Department of Hospital Comarcal de Riotinto. Adult patients (≥18 y) presenting with abdominal pain will be included. Both groups will receive standard care. In the intervention group, bedside ultrasound will be performed by trained family physicians; in the control group, ultrasound will be performed by radiologists only if deemed necessary. The primary outcome is the improvement in quality of care, assessed through a reduction in emergency department length of stay, fewer basic radiology tests requested, and diagnostic concordance. Secondary outcomes include the need for additional diagnostic studies and the appropriateness of referrals, evaluated through 1-month follow-up and reconsultation.

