The sample will consist of patients over the age of 18 years presenting with abdominal pain in the emergency department, who will be assigned to the experimental group (POCUS is performed) or the control group (no clinical ultrasound is performed) consecutively. Patients readmitted for the same pathology will be ruled out. Patients will be invited by the investigators to participate freely, and the recruitment will end when the minimum sample size is reached in each cohort.

The inclusion and exclusion criteria are presented in Textbox 1.

Textbox 1.The inclusion and exclusion criteria.

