**Figure 1. F1:**
[figure not shown]
Flowchart depicting study protocol. POCUS: point-of-care ultrasound.

Subjects will be observed for a period of 1 month to determine whether they have returned for a repeat consultation for the same reason, and if so, to check the degree of alignment of the final diagnosis with the initial care. Only in cases where the process is not resolved can the patient be monitored for the next 6 months.

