g CT: computed tomography.

h ED: emergency department.

Table 3 shows the results of the satisfaction questionnaire based on the SERVPERF model.

**Table 3. T3:** Satisfaction questionnaire based on the SERVPERF model^a^.

Dimensions and questions		Score range (strongly disagree to strongly agree)
Tangible elements		
	The facilities are suitable for patient care	1-7
	Technological equipment is adequate	1-7
	The emergency department has sufficient capacity to attend to the population	1-7
Responsiveness dimension		
	If you have any questions, you will receive a response within a reasonable time	1-7
	The attention of the staff provides a fast and high-quality service	1-7
	You have been dealt with quickly and promptly	1-7
Reliability dimension		
	When staff commit to doing something within a certain time frame, it is fulfilled	1-7
	If you have a problem, the staff show an interest in solving it	1-7
	Staff perform the service well the first time	1-7
	Professionals are ready to help when they are needed	1-7
Security dimension		
	Staff behavior imparts confidence	1-7
	There is a capacity to resolve doubts accurately	1-7
	Staff are knowledgeable when responding to queries	1-7
Empathy dimension		
	Care is offered that responds to the needs of the users	1-7
	Staff care about your interests and needs	1-7
	The emergency service provides a solution to the health needs of users	1-7
Access dimension		
	The waiting time for service was adequate	1-7
	Waiting time for tests and results was adequate	1-7
	The overall waiting time was adequate	1-7

a Likert scale (1-7) from least to most satisfaction.

Table 4 shows the work schedule for the study protocol.

Potential harms will be defined as any adverse event or unintended consequence resulting from the use of bedside ultrasound by nonradiologist physicians. Harms will be assessed systematically, using a structured reporting form completed by the attending physician and monitored through follow-up at 1 month. Any serious adverse events will be documented and reviewed by the principal investigator and the ethics committee if needed.

**Table 4. T4:** Timeline of the study.

		Year 1												Year 2											
	Phase 0	1	2	3	4	5	6	7	8	9	10	11	12	1	2	3	4	5	6	7	8	9	10	11	12
Ultrasound training	✓																								
Literature review update		✓																							
Presentation of the research project in the emergency department			✓																						
Protocol development				✓	✓																				

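### Harms are defined only as consequences of bedside ultrasound, so no control-group event can qualify and harms as defined cannot be compared between groups

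*Protocol article*

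**What the plan says.** The harms paragraph stands in the protocol article under Variables, just before Table 4. It limits potential harms to "any adverse event or unintended consequence resulting from the use of bedside ultrasound by nonradiologist physicians". They are to be assessed "using a structured reporting form completed by the attending physician and monitored through follow-up at 1 month". The paragraph ends: "Any serious adverse events will be documented and reviewed by the principal investigator and the ethics committee if needed".

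On exposure, Study Design and Setting describes the "control group (no clinical ultrasound is performed"). The Methods part of the abstract adds that "in the control group, ultrasound will be performed by radiologists only if deemed necessary". Textbox 1 has experimental patients seen by professionals with demonstrated training in clinical ultrasound, and control patients by professionals without it.

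On follow-up, the text after Figure 1 says: "Subjects will be observed for a period of 1 month to determine whether they have returned for a repeat consultation" for the same reason. For those who return, it adds a check of whether the final diagnosis agrees with the initial care. Diagnostic concordance is part of the primary outcome in the abstract and a yes/no item in Table 2. Neither is limited to one group. Table 2, presented as the full variable list, has no adverse event item.

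**The concern.** The hypothesised benefits are a shorter stay, fewer radiographs and fewer ultrasounds by radiologists. The natural counterweight to less work-up is a missed or delayed diagnosis. That can happen after a reassuring bedside scan, and it can also happen under usual care. A harm definition that names the scan as the cause records such events on one side only.

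The causal condition adds a second difficulty. A diagnostic test usually harms indirectly, through a decision taken on its result, and that link is hard to establish in a single patient. The definition nevertheless requires the link before an event is recorded, and the form is filled in by the treating doctor, who knows the group.

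The record matters because Study Design and Setting provides for no data monitoring committee and leaves participant safety to the investigators. The Discussion says favourable results could support standardised protocols for scanning by family physicians. A reader of the results will want to know whether the quicker pathway had as few bad outcomes as the usual one.

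**Working it through.** The plan gives no figure for harms, so there is none to reproduce. The main check sets the passages side by side. A short calculation then shows what a common definition could deliver at this sample size.

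**1. Can a control patient have a harm?**
- Condition in the definition: the event results from bedside ultrasound by a nonradiologist (Variables).
- Control exposure: no clinical ultrasound (Study Design and Setting), and ultrasound only by radiologists (abstract, Methods).
- The condition cannot be met. The control count is 0 of the planned 97, or 0 of the 84 minimum, with certainty. Any difference in defined harms equals the experimental-group rate: p_E − 0 = p_E. It carries no information about usual care.

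**2. Who decides that an event counts?**
- The attending physician completes the form (Variables).
- In the experimental group that doctor belongs to the ultrasound-trained staff (Textbox 1), and trained family physicians perform the scans (abstract). That the two are often the same person is an inference from these statements.
- Causation is part of the case definition, so whoever completes the form has to judge it before recording an event.

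**3. Do other data fill the gap?**
- Serious adverse events: the sentence says any, names no group and requires no causal link. It also closes a paragraph whose subject is ultrasound-caused harm. Both readings are possible.
- Reconsultation: all subjects, 1 month, limited to the same reason. The diagnosis check described there applies to those who return.
- Diagnostic concordance: all subjects, from follow-up or a second opinion.
- Death appears only among the reasons for discontinuation. Unplanned admission after the index visit is not a listed variable.

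Diagnostic error can therefore be compared to some extent, but the plan does not classify it as harm.

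**4. What would a common definition give?**
Inputs: 84 per group (stated minimum) and 97 per group (stated recruitment). The event rates of 5% and 10% are assumptions; the documents give none.
- Standard error of the risk difference: √[(0.05×0.95 + 0.10×0.90)/n] = √(0.1375/n), which is 0.0405 at n = 84 and 0.0377 at n = 97.
- 95% CI half-width, 1.96 × SE: about 7.9 and 7.4 percentage points, against an assumed difference of 5 points.
- Power, two-sided 5%: 23% at 84 and 26% at 97.
- Other assumed pairs, at 84 (97) per group: 2% vs 5%, 18% (20%); 5% vs 15%, 58% (64%); 5% vs 20%, 84% (89%).

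Only a large difference would be detected reliably, so the comparison would be descriptive.

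**The case against.** The strongest reply is that the paragraph describes monitoring of an added procedure in a study presented as minimal risk. No objective and no part of the Statistical Analysis section compares harm counts between groups. On that view a tally of scan-related events is legitimate, and the zero in the control group is simply what such a tally means. This stands in part: no planned analysis is contradicted.

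A reader might go further and infer that the trial cannot compare safety at all. The documents do not support that. Diagnostic concordance and 1-month reconsultation are collected without restriction to a group, and they address the most likely route of harm from a diagnostic test. The serious-event sentence may also cover controls.

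A reader might also infer that the harm count will point in the wrong direction. That would require a between-group harm comparison, and none is planned.

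On attribution, the article does not say that the attending physician judges causation alone. It adds 1-month monitoring, and review of serious events by the principal investigator and, if needed, the ethics committee. That softens the worry about operator judgement. It does not remove it, because an event not recognised as scan-related falls outside the definition.

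Finally, the content of the reporting form may properly sit in a fuller protocol. The definition itself, however, is stated in the article and is one-sided as written.

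**Conclusion.** The point holds in a limited form. Harms as defined cannot occur in the control group, so their count there is 0 of 97 by construction and cannot be compared with the experimental group. This follows from the wording and needs no assumed rate. Attribution is built into the definition and falls first to the attending physician; that this is often the operator is a reasonable inference, not a stated fact. The scope of serious adverse event collection is unclear.

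Some comparison of diagnostic error remains possible through concordance and reconsultation, although the plan does not treat these as harm outcomes. The primary analysis of length of stay is unaffected. The definition should be changed because a better one is available at small cost. Even then, the comparison would be imprecise (about 25% power for an assumed 5% vs 10%) and open to confounding, since the groups are not randomised.

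**What to change.** - Define adverse events in the same words for both groups and without reference to cause: for example, missed or delayed diagnosis, unplanned return, unplanned admission or death within 1 month of the index visit.
- Complete the structured form for control patients as well, and add the item to Table 2.
- State that serious adverse events are documented and reviewed in both groups.
- Keep the physician's judgement of scan-relatedness as a separate descriptor that does not decide whether an event is recorded.
- Say how diagnostic concordance and reconsultation feed into the harm outcome, so that the same event is not handled under two rules.
- Report counts and a risk difference with 95% CI by group, labelled descriptive, with a note on low precision and nonrandomised groups. No hypothesis test or change in sample size is needed.

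The cost is a reworded paragraph and a little extra form completion for controls. The 1-month observation already covers all subjects. Because recruitment is described as ongoing, the change should go to the ethics committee as a protocol modification if it is judged significant. The report should also say which patients were enrolled before it took effect.

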### Ethical Considerations

This study has been approved by the Huelva Provincial Independent Ethics Committee (reference code PEIBA 1923-N-21). Any significant modifications to the protocol will be submitted for approval to the same ethics committee and promptly communicated to all relevant stakeholders, including participating investigators and, where necessary, trial registries.

Informed consent will be obtained by the attending family physicians or authorized research team members prior to the inclusion of any participant. Participants will receive both oral and written information about the study objectives, procedures, risks, and benefits and will be given the opportunity to ask questions before providing written consent. No biological specimens will be collected, and no ancillary studies requiring additional consent are planned. Participants will not receive any financial compensation or incentives for their participation in the study.

Personal data will be collected and stored using anonymized codes to ensure confidentiality. Access to identifiable information will be restricted to the research team and stored securely in password-protected systems in accordance with national data protection regulations. Data will be treated with strict confidentiality before, during, and after the trial, and only aggregated, deidentified data will be reported in publications or presentations.

Given the minimal-risk nature of this study, no specific post-trial care provisions are foreseen. However, if any harm were to occur as a result of participation, appropriate medical care and any necessary support will be provided by the institution in accordance with applicable regulations and institutional policies. The application procedures and the study were approved by the Huelva Provincial Ethics Committee (Comité de Ética de Investigación de Huelva) (Code PEIBA 1923-M1-21).

## Results

The first phase of the project began in 2023 with the validation of the data collection form. Subsequently, the patient satisfaction questionnaire was validated, and the results were published in the journal Care Primary. The study has received external funding, and patient recruitment is currently ongoing and expected to be completed in December 2025.

The project was initiated in 2023. Between March and July 2023, an initial validation phase of the data collection form was conducted. Preliminary findings were presented as a clinical communication at the 44th semFYC National Congress, held in Barcelona, 14‐16 November 2024. A total of 65 patients were included in this first sample, with a mean age of 56.6 (SD 20.0) years, of whom 53.8% (n=35) were women and 46.2% (n=30) were men. The validation of the data collection form showed that 76.9% (n=50) of the ultrasound examinations were performed as point-of-care clinical ultrasounds (POCUS), whereas only 6.2% (n=4) were formal imaging studies referred to the Radiology Department.

Based on this pilot experience, the study protocol was further developed. Funding was subsequently obtained through the 2024 Call of the Fundación Progreso y Salud (Andalusian Public Health System) under the Research and Innovation Projects category in Primary Care, Regional Hospitals, and High-Resolution Healthcare Centers (grant ID: AP-0561‐2024-C5-F2).

Further work focused on refining the study protocol and validating the patient satisfaction questionnaire was published in [31].

Patient recruitment is currently ongoing and is expected to be completed by December 2025. We anticipate that the implementation of POCUS in patients presenting with abdominal pain in emergency settings will lead to a reduction in length of stay and a decrease in the use of additional diagnostic tests, such as plain radiography or formal radiology−performed ultrasound.

## Discussion

### Principal Findings

POCUS has emerged as a valuable tool in emergency medicine, particularly for its potential to reduce diagnostic uncertainty and enhance clinical accuracy in decision-making. Despite these recognized advantages, there is limited evidence regarding its overall impact on the quality of care, and even less from the patient’s perspective. This study protocol is based on the hypothesis that the implementation of clinical ultrasound performed by family physicians in emergency departments can reduce length of stay and decrease the need for complementary diagnostic tests, such as plain radiography or radiology-performed ultrasound. Collectively, these improvements may lead to a measurable enhancement in both perceived and actual quality of care.

The geographic context of this study adds a relevant dimension to the analysis. The target population resides in an area characterized by wide territorial dispersion and significant population aging, factors that place additional demands on emergency services. In such settings, clinical practice often prioritizes the resolution of health problems in a single visit to avoid repeated travel—especially for patients with reduced mobility or limited access to transportation. POCUS performed by emergency physicians may therefore not only optimize diagnostic workflows but also align more closely with the health care needs of the community.

One of the main methodological challenges in this study is interoperator variability in the interpretation of ultrasound findings. To minimize this, a reference image repository has been developed, alongside simplified visual guides to standardize the use of clinical ultrasound in patients presenting with abdominal pain. In addition, prestudy training sessions were conducted in collaboration with the radiology department to promote consistency in image acquisition and interpretation among participating physicians.

Beyond evaluating diagnostic efficiency, the study also aims to identify the key factors contributing to improved quality of care from the health care professional’s perspective. This approach will provide both qualitative and quantitative insights into the clinical, organizational, and human elements that influence better health outcomes.

Finally, this research initiative may pave the way for broader applications of clinical ultrasound beyond hospital-based emergency settings, including prehospital care and primary health care services. If the results are favorable, they could support the development and implementation of standardized protocols for the use of POCUS by family physicians, with potential implications for health care system efficiency and patient-centered outcomes.

### Conclusion

This study aims to assess whether the implementation of POCUS performed by family doctors in the emergency department reduces the length of stay in the department, as well as other diagnostic tests such as simple radiology or regulated ultrasound, improving the quality of patient care.
